### Study design and experimental procedures

This pragmatic parallel-group RCT will compare two 12-week interventions and includes four evaluation sessions over 26 weeks (baseline, week 6 [mid-intervention], week 12 [end of intervention] and week 26). Once the written informed consent form will have been signed and eligibility criteria confirmed by an independant PT, participants will take part in the baseline evaluation. At baseline, participants will first complete a questionnaire on sociodemographic, symptoms and comorbidity. Then, they will be randomly assigned to either the 1) group-based supervised training program or 2) usual individual physiotherapy care. They will then take part in their assigned 12-week intervention at the Valcartier Health Centre (Fig. 1). At follow-up evaluations, the primary and secondary outcomes will be assessed using web-based questionnaires integrated within the Research Electronic Data Capture platform (REDCap) [34]. This pragmatic randomized controlled trial protocol have bee registered on clinicaltrials.gov (NCT05235152) [35].

**Fig. 1 Fig1:**
[figure not shown]
Study design

### Randomisation/blinding

A randomisation list will be established using a computer random number generator (sealedenvelope.com) prior to the initiation of the study by an independent research assistant. Allocation will be concealed in sealed and sequentially numbered opaque envelopes. Randomisation will be stratified by sex and type of MSKd to ensure balance of the treatment groups with respect to these variables. A blocked randomisation (random blocks of 3 or 6) will also be used to make sure that two equal groups of 60 participants (15 participants/diagnosis) will be obtained. Given that for this type of intervention it is impossible to blind the treating PT and participants, only the evaluator and statistician will be blinded. To reduce potential contamination bias, the two interventions will be given in different closed rooms at the Valcartier Health Centre by different PTs. Participants will be instructed to avoid discussing their group assignment or interventions with other participants or with the evaluator.

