### Sample size

Based on our sample size calculation, calculated for our primary outcome (Pain Interference subscale of the Brief Pain Inventory) using data from a pilot study on military members with MSKd [33], 15 participants per diagnosis will be required per group for a total of 120 participants (60 participants/group) (G*Power 3.1.7; α = 0.05, 1-β = 0.95, Baseline mean: 2.9+/− 1.5 points, Follow-up mean: 0.8+/− 1.2 points, expected lost at follow-up = 15% [based on past experiences with this population]. This number will enable us to determine the effects of the interventions for each of the four conditions.

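### Random blocks of 3 or 6 cannot guarantee two equal arms, because a block of 3 always splits 2:1 or 1:2; the practical effect is small

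*Protocol article*

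**What the plan says.** All statements are in the protocol article.

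- **Study design and experimental procedures** describes two arms: "they will be randomly assigned to either the 1) group-based supervised training program or 2) usual individual physiotherapy care".
- **Randomisation/blinding** adds stratification: "Randomisation will be stratified by sex and type of MSKd to ensure balance of the treatment groups with respect to these variables". Two sexes by four diagnoses gives 8 strata.
- The same section gives the block sizes and their purpose: "A blocked randomisation (random blocks of 3 or 6) will also be used to make sure that two equal groups of 60 participants". It finishes the thought by saying that "two equal groups of 60 participants (15 participants/diagnosis) will be obtained".
- **Sample size** sets the same target: "15 participants per diagnosis will be required per group for a total of 120 participants (60 participants/group").

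The article mentions no third arm, no unequal ratio, and no rule that pairs a 2:1 block with a 1:2 block.

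**The concern.** With 1:1 allocation to two arms, a block can be balanced only if its size is even. A block of 6 can hold three of each arm. A block of 3 cannot be balanced, whatever the software does with it. The method and the purpose given for it stand in one sentence and do not fit together.

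This is not a detail left to a fuller document. The article states the block sizes, and states a pair of which one cannot do the job claimed for it.

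What is at stake is mainly balance within diagnosis. The Sample size section counts on 15 per arm per diagnosis to assess each condition, and cells that small feel a shift of two participants more than the pooled comparison does. The allocation procedure should also be one that can be carried out and described as written.

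**Working it through.** **1. The plan's target.** 15 per diagnosis per arm × 4 diagnoses × 2 arms = 120, or 60 per arm. The 15 can be reproduced from the Sample size section: "α = 0.05, 1-β = 0.95" and "Baseline mean: 2.9+/− 1.5 points, Follow-up mean: 0.8+/− 1.2 points". Treating the two means as two independent groups with a two-sided test (the article states neither), the pooled SD is √((1.5² + 1.2²)/2) = 1.358 and the difference is 2.9 − 0.8 = 2.1. A two-sample t-test then needs 12 per cell. With 15% loss, 12/0.85 = 14.1, rounded up to 15. The target is therefore clear and is not in question here.

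**2. Block arithmetic.** 3/2 = 1.5, so a 3-block is 2:1 or 1:2. 6/2 = 3, so a 6-block is 3:3.

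**3. A bound by hand.** Take blocks of 3 only, each direction with probability ½, and ignore sex strata. Each diagnosis has 30/3 = 10 blocks, each adding +1 or −1 to the arm difference.
- Exactly 15/15 in a diagnosis: C(10,5)/2¹⁰ = 252/1024 = 24.6%.
- Over 40 blocks, the SD of the arm difference is √40 = 6.3.
- Exactly 60/60: C(40,20)/2⁴⁰ = 12.5%. Simulation of this case gave an SD of 6.35 and 12.3%.

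**4. Blocks of 3 and 6 mixed, by simulation.** Assumptions, none of them in the article: sizes 3 and 6 equally likely, direction of each 3-block random, 30 participants per diagnosis, and men/women per diagnosis from 20/10 to 27/3. The even-block comparison uses sizes 4 and 6, equally likely.

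| Result | Blocks 3 and 6 | Blocks 4 and 6 |
|---|---|---|
| Exactly 15/15 in a diagnosis | about 33–39% | about 47–65% |
| 17/13 or worse in a diagnosis | about 14–20% | about 1–3% |
| Exactly 60/60 overall | about 15–20% | about 26–33% |
| 15/15 in all four diagnoses | about 1–2% | about 5–19% |
| Central 95% range of arm size (widest case) | 55 to 65 | 57 to 63 |

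**5. Cost in precision.** The variance of a difference in means, relative to equal arms, is (1/n₁ + 1/n₂) divided by its value at equal arms.
- 65/55 overall: (1/65 + 1/55)/(2/60) = 1.007, an increase of 0.7%.
- 17/13 in one diagnosis: (1/17 + 1/13)/(2/15) = 1.018, an increase of 1.8%.

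**6. What even blocks leave over.** Every completed even block is 1:1, so the remaining imbalance comes only from the unfinished last block in each of the 8 strata. Blocks of 6 alone, with an assumed 24/6 sex split, gave 60/60 and 15/15 in every run, because 24 and 6 are multiples of 6. With 25/5, 60/60 occurred in only about 27% of runs under every even scheme tried.

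**The case against.** The strongest case on the other side is that the consequences are minor, and most of it stands.

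- If the direction of each 3-block is random, every participant still has an even chance of either arm. No bias arises.
- Allocation is concealed in sealed, numbered, opaque envelopes, and the planned GEE analysis does not need equal arms.
- The precision loss is of the order of 1–2% at the unfavourable end.
- The primary analysis pools the diagnoses, and the comparisons by condition on the region-specific questionnaires are labelled exploratory. A 16/14 or 17/13 cell defeats neither.
- Even blocks do not secure exact equality either. Part of the shortfall comes from eight strata with incomplete last blocks.
- The 3 may simply be a misprint.

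None of this removes the contradiction, but it does fix its weight.

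A reader might go further and infer three things that the article does not support. The first is that the list cannot be generated: it can, with each 3-block filled 2:1 or 1:2. The second is that the arms will certainly be unequal: equal totals still occur by chance in about 15–20% of runs. The third is that the trial is in effect 2:1, ending at 80/40 with a variance (1/80 + 1/40)/(2/60) = 1.125 times that of equal arms. That contradicts the stated 60 per group, and it needs the 6-blocks filled 4:2 although they divide evenly. Even if only the 3-blocks were fixed in one direction, with sizes equally likely, the expected arms would be about 67/53 and the variance increase about 1.3%.

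**Conclusion.** The point holds as an internal inconsistency: blocks of 3 cannot guarantee the equality that the blocking is said to ensure. This follows from the article's own figures and needs no assumption. The size of the effect does rest on assumptions, namely an equal mix of block sizes, random direction of the 3-blocks and a sex split that the article does not give. Over the splits tried, blocks of 3 raise the frequency of a 17/13 or worse split within a diagnosis from about 1–3% to about 14–20%, and widen the range of arm size from about 57–63 to about 55–65.

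Validity is not threatened and power is barely touched. This is a lower-severity correction, worth making because it is cheap and because imbalance is hard to repair once allocation is complete.

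**What to change.** 1. Have the independent research assistant who prepared the list confirm the block sizes actually used.
2. If 3 is a misprint, correct the text.
3. If it is not, regenerate the unused part of the list with even block sizes (for example 4 and 6) within the sex-by-diagnosis strata, and document the ratio realised so far.
4. In either case, replace the promise of two equal groups with one of approximately equal groups, overall and by diagnosis, since unfinished last blocks in 8 strata prevent a guarantee even with even blocks.

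The cost is one check and one sentence or, at most, a new computer list and the remaining envelopes. Sample size and analysis are unaffected.

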### Interventions

Before randomization, all participants will be evaluated by a PT (i.e., individual evaluation) [36, 37]. Then, participants will be randomized and will take part in their assigned 12-week intervention, which will consist of a maximum of 16 in-person sessions of 30 to 45 min each. An individualized home exercise program lasting 20–30 min, to be performed 3–4 times per week, will also be given to the participants in both groups.

If participants are symptom-free or do not have any functional limitations left before the end of the 16 sessions or 12 weeks, treatment will be ceased as judged by the PT supervising the group-based interventions or the individual treatment. The home exercises program will then be continued, with the possibility to resume the intervention if there is a recurrence of pain or functional limitations within the 12-week intervention period.

#### Usual individual physiotherapy care (UPC)

PTs will be asked to provide UPC that best reflects usual physiotherapy interventions at the physiotherapy clinic of the Valcartier Health Centre, that is an education-based (e.g., physiopathology, pain management, activity modification, reassurance, basic pain neuroscience, pain related fears, pain catastrophizing) [38], active exercise rehabilitation approach which includes strengthening and neuromuscular training exercises (including proprioception). In addition, interventions targeting mobility (stretching; active, active-assisted, passive range of motion exercises; repeated movements [Mulligan or McKenzie]) and manual therapy will be used as recommended in clinical practice guidelines [36, 37]. Patients will thus receive the treatments they would normally receive, and interventions will be selected according to PT’s and patients’ preferences.

#### Group-based supervised training program

The low back pain, upper extremity and lower extrimity Training Programs were developed for military members with MSKd by the Valcartier Health Centre PTs based on a literature review and clinical experience [20, 21]. These group-based training programs have been implemented and used for several years in addition to individual physiotherapy to increase the number of patients managed. They are composed of stations that each include several exercices of varying levels of difficulty (see further description below). Group size will vary between 5 to 20 participants for one PT or PT technologist, and each military member performs his/her own exercices. For example, during a typical session, the participant and PT will choose one exercise to perform per station according to two main criteria: severity of the condition (i.e., symptoms and limitations) and the ability to perform the exercises optimally. The level of supervision will be adapted to the participant’s needs and performance. Exercises are progressed if the quality of movement control is considered adequate by the PT and the exercise is no longer a challenge according to the participant. Exercise parameters and progressions of the programs have been chosen to increase strength, endurance and neuromuscular control [39, 40]. Progression in the programs leads to the execution of exercises that simulate functional and occupational tasks (task-oriented approach with gradual exposure) [21]. In accordance with recognized motor learning principles, participants will be encouraged to complete a large variety of exercises and to focus on the quality, rather than the quantity of their movements [41]. Exercises will be paused if pain is greater than 3/10 during execution or if fatigue results in compensatory movements [42].

The Lumbar Training Program is composed of 7 stations. The exercises are grouped together as follows: hip strengthening and control; the squat and its variants; elastic bands and the body blade; abdominal planks and their variants; abdominal strengthening; back extensor strengthening; and lifting techniques [20]. The Upper Extremity Training Program for rotator cuff-related shoulder pain is composed of 10 stations. The stations include postural and scapulothoracic control; weight bearing exercises; neuromuscular re-education of the rotator cuff complex; serratus anterior strengthening; trapezius strengthening; body blade exercises; proprioception and motor control exercises; functional activities; push-ups, bench press and sand bad lift [21]. The Lower Extremity Training Program for patients with pattelofemoral pain syndrome and lateral anke sprain is also composed of 10 stations. The stations include static one-leg balance; hip control exercises; jump landing; BOSU exercises (jumping consecutively on top of, and then on the other side of the BOSU); one-leg side jumping; jumping on stones; trampoline exercises; stability exercises; static and dynamic balance exercises on a beam; dynamic control exercises [43–45].

### Outcomes

The primary outcome will be functional limitations, as measured with the Pain Interference subscale of the Brief Pain Inventory – Short Form (BPI). The secondary outcomes will include pain severity as measured with the Pain Severity subscale of the BPI, and health-related quality of life as measured with the EQ-5D-5L. As pain-related fear has been shown to influence outcomes in military members and conservative management reduces pain-related fears [20, 46], both interventions will also be compared on their impact on pain-related fears, measured with the Tampa Scale for Kinesiophobia (TSK) [38]. Furthermore, region-specific symptoms and functional limitations will be assessed using the Oswestry Disability Index (ODI) for low back pain, the shortened version of the Disabilities of the Arm, Shoulder and Hand (*Quick*DASH) for rotator cuff-related shoulder pain, Knee Outcome Survey Activities of Daily Living Scale (KOS-ADLS) for patellofemoral pain syndrome and Lower Extremity Functional Scale (LEFS) for lateral ankle sprain. To monitor compliance with home exercises, participants will be asked to maintain a weekly web-based logbook on RedCap during the 12 weeks of the intervention. Finally, participant’s satisfaction with treatment will be assessed at the end of the treatment (i.e., week-12) (see bellow for further description).

#### Functional limitations

The BPI is an 11-item questionnaire designed to evaluate the intensity of, and the impairment caused by pain. Originally developed to evaluate cancer pain, the BPI has since been shown to be a valid, reliable and responsive instrument for MSKd [47–50]. The Pain Interference subscale is recommended for assessment of pain-related functionnal limitations and includes seven items that measure the level of interference with function caused by pain using 0 (no interference) to 10 (complete interference) rating scales [49, 50].

### Pain severity

The Pain Severity subscale of the BPI includes four items that measure pain intensity using 0 (no pain) to 10 (pain as bad as you can imagine) rating scales [51].

### Health-related quality of life

The EQ-5D-5L is a generic health-related quality of life (HRQoL) questionnaire that contains five questions covering five dimensions: mobility, self-care, usual activities, pain/discomfort and anxiety/depression. Each question is rated on a five-point scale from 1 (no problems) to 5 (unable to perform). The combined dimensions describe 5^5^ = 3125 theoretically possible states of health that can be converted into a weighted index score ranging from 0 to 1. Its validity, reliability and responsiveness (CID = 0.32 point) have been established for MSK conditions [52, 53].

### Pain-related fear

The Tampa scale of kinesiophobia (TSK) is a 11-item scale measuring beliefs and behaviours related with pain, specially focusing on beliefs that pain is damaging and painful movements should be avoided [42]. Its psychometric properties have been shown for different MSKd [43].

### Region-specific symptoms and functional limitations

#### For low back pain

The modified ODI is a 10-item questionnaire that assesses the interference of low back pain with activities of daily living. Its reliability (MDC = 10 points), construct validity and responsiveness to change (CID ranges from 10 to 14) have been demonstrated [23, 54–57].

#### For patellofemoral pain syndrome

The KOS-ADLS (MDC90 = 8.3 points; CID = 13.6 points) is a 14-item knee-specific questionnaire that evaluates symptoms and functional limitations experienced during activities of daily living in individuals with various knee disorders [58].

#### For rotator cuff-related shoulder pain

The *Quick*DASH (MDC = 11%, CID = 10 points) is an 11-item questionnaire addressing the level of difficulty in performing daily activities and the severity of the symptoms of the upper limbs [59]. It has been validated in individuals with rotator cuff-related shoulder pain [30].

#### For lateral ankle sprain

The LEFS is a 20-item questionnaire assessing the impairment of the lower-extremity MSK system in everyday activities [60]. It has been validated in individuals with lateral ankle sprain, and its reliability, construct validity and responsiveness have all been demonstrated (MDC and CID are both 6 points) [61].

### Satisfaction

Patients satisfaction with treatment will be assessed at 6 and 12 weeks using the Patient Acceptable Symptom State (PASS) [62, 63], It asks patients weither they are satisfied with their current state or not and to rate their satisfaction on a 0–10 numeric scale (0 representing not satisfied at all, and 10 very much satisfied) [49]. They will also be asked to rate their satisfaction with treatment received using a three-item Likert scale (“not satisfied”, “satisfied” or “very much satisfied”), their satisfaction with the frequence of treatments (“not enough”, “just right” or “too much”), their satisfaction with the duration of treatments (“too short”, “long enough”or “too long”) and their satisfaction with the time spent with the PT during the treatments (“not enough”, “just right” or “too much”) [49, 51, 64].

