**Methods:**

One hundred and twenty soldiers with a new medical referral for physiotherapy services for one of the four targeted musculoskeletal disorders will be consecutively recruited. They will be randomly assigned to either group-based training program or usual individual physiotherapy care, and will take part in the assigned 12-week intervention. There will be four evaluation sessions over 26 weeks (baseline, week 6, 12 and 26). At each follow-up, functional limitations, pain severity, health-related quality of life and pain-related fears will be assessed. Patients satisfaction with treatment will also be evaluated at the end of the intervention period. Either two-way repeated measures ANOVA will be used to analyse and compare the effects of the interventions.

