Physical rehabilitation among military members with MSKd requires innovative effective interventions to optimize the use of ressources and increase access to these services. As the literature encourages the use of active exercises for the management of MSKd [4, 16], the development of a tailored supervised group-based exercise approach could represent an option of choice. Supervised group-based exercise programs have been shown to reduce wait times to rehabilitation services [17] and to be effective in the management of MSKd [18]. However, the majority of studies until now have evaluated group-based interventions for chronic low back pain [18]. In the last 10 years, three supervised group-based exercise programs supervised by physiotherapists (PT) and physiotherapy technologists (Phys. T.) have been developed at one of the Canadian Armed forces (CAF) bases (Valcartier) (Lumbar Training Program for for low back pain; Upper Extremity Training Program for rotator cuff-related shoulder pain; Lower Extremity Training Program for patellofemoral pain syndrome and lateral ankle sprain). They were developped to increase access to physical rehabilitation care regarding the most prevalent MSKd, as CAF statistics show the lumbar spine, knee, ankle and shoulder are by far the most frequently affected body parts, contributing to 58.2% of all cases of MSKd [15, 19–21]. Although these group-based exercise programs have been widely used, their clinical effectiveness needs to be evaluated in large samples or compared to usual individual physiotherapy care (UPC).

The primary objective of this pragmatic randomized controlled trial [22] is to evaluate the mid- and long-term effects of group-based supervised training programs on pain severity and functional limitations, in comparison with UPC in the treatment of military members presenting common MSKd. Secondary objectives include comparing both interventions 1) in terms of health-related quality of life, 2) pain-related fear, and 3) satisfaction with care received. We hypothesize that the group-based supervised training programs will be at least as effective as UPC to decrease functional limitations and pain severity, to improve health-related quality of life and pain-related fears and participants will be equally satisfied with both interventions.

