### Statistical analyses

Descriptive statistics will be used for all outcome variables at each measurement time to summarise results. Baseline demographic data will be compared (independent *t*-tests and Chi-squared tests) to establish the comparability of groups. An intention-to-treat analysis will be used in which all participants will be analysed in the group to which they were assigned. In addition, sensitivity analyses will also be performed using per-protocol analyses; these analyses will allow to verify the consistency of the results in participants strongly compliant with the interventions (e.g., 75% attendance and home exercises). All dropouts and the reason for dropping out of the study will be reported. Any harm or unintended effects and co-interventions will be recorded. A 2-way ANOVA (2 Interventions [Group-Based or UPC] × 4 Times [0, 6, 12, 26 weeks]) will be used to analyse and compare the effects of the interventions on the primary outcome (Pain Interference Scale) and on four of the secondary outcomes (Pain intensity subscale, EQ-5D-5L, TSK) (SPSS, proc. GENLIN [Generalized Estimating Equations – GEEs]). Effect sizes (Cohen’s *d* for between-groups comparisons, Glass’s Δ for within-group comparisons) will be calculated. Nonparametric Analysis for Longitudinal Data (nparLD Package 2.1, R-software, v.3.6.1) will also be considered in cases where GEEs are not applicable (undefined distributions). If nparLD are used, effect sizes will be reported as relative treatment effect. Satisfaction with treatment will be compared between the two interventions using Chi-squared test for the PASS and Mann Whitney test or independent *t*-tests for satisfaction questions using the Likert scales. Exploratory analyses (using a similar statistical approach as for primary outcome) will be performed to compare the two interventions for each of the four conditions using the region-specific questionnaires (ODI, KOS-ADLS, *Quick*DASH, LEFS).

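### The PASS, which the protocol describes as a question about the patient's current state, is labelled and tested as satisfaction with treatment, and the visits for satisfaction do not agree

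*Protocol article*

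**What the plan says.** **Objective.** The last paragraph of the Background lists the secondary objectives, ending with "2) pain-related fear, and 3) satisfaction with care received". The matching hypothesis is that "participants will be equally satisfied with both interventions".

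**Instrument.** The Satisfaction section states: "Patients satisfaction with treatment will be assessed at 6 and 12 weeks using the Patient Acceptable Symptom State (PASS"). Its description of the instrument follows: "It asks patients weither they are satisfied with their current state or not and to rate their satisfaction on a 0–10 numeric scale". The same section then adds four direct questions, each with three response categories: satisfaction with the treatment received, with its frequency, with its duration, and with the time spent with the physiotherapist.

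**Visits.** The Methods part of the abstract says "Patients satisfaction with treatment will also be evaluated at the end of the intervention period". The Outcomes section says "satisfaction with treatment will be assessed at the end of the treatment (i.e., week-12"). The Satisfaction section gives weeks 6 and 12, as quoted above.

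**Analysis.** The Statistical analyses section says "Satisfaction with treatment will be compared between the two interventions using Chi-squared test for the PASS". The same sentence assigns a Mann-Whitney test or independent t-tests to the Likert-scale satisfaction questions. No visit is named for any of these tests.

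**The concern.** There are two separate problems.

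The first is what the PASS measures. The objective is about the care, but the question as the protocol describes it is about how the patient is now. The two arms differ mainly in delivery: groups of 5 to 20 under one physiotherapist or technologist, against individual care. A patient can be content with the current state of the shoulder or back and still dislike being treated in a group, or the reverse. The trial also hypothesises that the group programmes are at least as effective as usual care. If recovery is similar in the two arms, the PASS would tend to be similar too, whatever participants think of group delivery. Reporting that similarity as equal satisfaction with treatment would claim more than the question can support. A difference on the PASS would, in turn, largely reflect symptoms, which overlap with the pain and function outcomes already in the plan.

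The second is when satisfaction is measured. One section includes a mid-treatment assessment that the other two leave out, and the tests planned for satisfaction take one time point. As the sections stand, it is not settled which data enter the comparison.

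**Working it through.** No figure in the protocol bears on this point and no formula applies, so the check is a comparison of text.

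**Step 1: what is asked and what it is called.**

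| Place | Content | Object of the satisfaction |
|---|---|---|
| Background, secondary objective 3 | Objective | Care received |
| Satisfaction, opening statement | PASS introduced as the measure | Treatment |
| Satisfaction, description of the PASS | Yes/no question, with a 0–10 rating | Current state |
| Satisfaction, later questions | Four direct items | Treatment received, frequency, duration, time with the physiotherapist |
| Statistical analyses | Chi-squared test on the PASS | Labelled as treatment |
| Statistical analyses, same sentence | Mann-Whitney or t-tests on the Likert items | The direct items |

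The second and third rows describe the same instrument but give it different objects. The description says what the patient is actually asked, so it determines what the answer means. The chi-squared comparison is therefore a comparison of symptom state. The only questions whose stated object matches the objective are the direct items, and the one on the treatment received is closest to its wording.

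**Step 2: visits.**

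| Place | Week 6 | Week 12 |
|---|---|---|
| Abstract, Methods | not included | included (end of the intervention period) |
| Outcomes | not included | included (given explicitly) |
| Satisfaction | included | included |
| Statistical analyses | not stated | not stated |

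The Study design section defines week 6 as mid-intervention and week 12 as end of intervention, so the phrase about the end of treatment cannot be stretched to cover week 6. That section's general sentence that primary and secondary outcomes are assessed at follow-up evaluations does not resolve the matter, because the Outcomes section gives a specific visit for satisfaction. Week 12 is the only visit found in all three descriptions.

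**Step 3: consequence for the analysis.** BPI pain interference, BPI pain severity, EQ-5D-5L and TSK go into a model over four times (0, 6, 12 and 26 weeks). Satisfaction is left out of that model and gets tests that compare two groups at one time. If the Satisfaction section is right, two sets of responses are available for a one-visit test.

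**The case against.** The strongest reply is that care satisfaction is measured and tested directly. The four direct items stand in the same section as the PASS and are compared between arms in the same sentence of the analysis. This stands, and it limits the point. A reader might infer that the objective rests on the PASS alone, so that a real difference in care satisfaction alongside equal recovery would go undetected. The documents do not support that: dislike of group delivery could show in the item on treatment received or in the one on time with the physiotherapist. What remains is that the PASS result is filed under the wrong name.

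A reader might also infer that two visits inflate the false-positive rate. The documents do not support this either. They nowhere say that both visits will be tested, or that one will be selected. Moreover, the hypothesis is equal satisfaction, so counting any difference at either visit would work against the investigators' expectation. The more relevant risk with an unfixed visit would be leaning on whichever one shows no difference, and nothing in the text says that is intended.

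On the visits, it can be said that neither the abstract nor the Outcomes section uses the word only, that the Outcomes section refers the reader to a fuller description below, and that the weeks in the Satisfaction section are attached to the PASS and not to the direct items. One could therefore suppose that the PASS is taken twice and the direct items once. That is possible, but the protocol does not say it, and the Outcomes section equates the assessment of treatment satisfaction with week 12. It is also fair that naming the analysis visit for a secondary outcome is often left to an analysis plan, which is not shown here. The missing visit alone would be no finding. The conflicting schedule is one, because an analysis plan would inherit it.

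Finally, choosing a single lead item for the objective is partly a matter of preference. The fix therefore relies on the direct items as a set and notes only which comes closest.

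**Conclusion.** The point holds in a limited form. The protocol assigns a question about current state to an objective about care received, and its three descriptions of when satisfaction is assessed do not agree. A PASS comparison from this trial would be informative about symptom state and should not be cited for or against equal satisfaction with the two interventions. The direct items can serve that purpose and are already planned.

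The importance is low. The matter concerns a secondary objective, and the sample size and the analysis of the primary outcome are untouched. No numerical size is attached, because the fault lies in labelling and scheduling, not in an error rate. The conclusion rests on taking the protocol's own account of the PASS at face value and uses no outside source on the instrument.

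**What to change.** - In the Satisfaction and Statistical analyses sections, report the PASS as a separate symptom-state outcome and stop presenting it as satisfaction with treatment.
- Base the third secondary objective on the existing direct items, noting that the one on the treatment received is the closest match.
- Name week 12, the visit common to all three descriptions, as the analysis visit for the satisfaction comparisons. If week-6 responses are collected, call them descriptive.
- Make the abstract, the Outcomes section and the Satisfaction section state the same schedule.

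The cost is a wording change; no new data are needed. The downside is that the item on the treatment received has only three levels, so it separates the arms coarsely.
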